### Investigation outcomes

Relevant investigations will be documented for each participant at the baseline clinic attendance, after 6 weeks and after 6 months. This will include: an exercise electrocardiographic stress test; nuclear medicine imaging - myocardial perfusion imaging; stress echocardiography; invasive coronary angiography; and noncardiac investigations, for example, endoscopy.

This will be documented by the clinician in charge of patient care in response to the CT coronary angiogram report. Further information will be obtained from electronic hospital records and patient surveys. Computed tomography coronary angiography will be performed prior to any invasive coronary angiogram, to facilitate a decision to undertake or cancel this invasive investigation.

### Treatment outcomes

All treatments will be documented at baseline, after CT scan (where appropriate), and at 6 weeks and 6 months. Documentation of current prescribed medications will be obtained from patients, electronic hospital records or general practitioners. This will include:

1. * Secondary prevention.* Prescription of drug therapy for the prevention of cardiovascular events will be documented; drugs listed will include aspirin, clopidogrel, other anti-platelet agents, statins, angiotensin-converting enzyme inhibitor therapy, and beta-blockers.

2. * Pharmacological anti-anginal therapy.* Prescription of drug therapy (drug, class, dose) for the alleviation of angina pectoris will be documented; this will include beta-blockades, calcium antagonists, nitrates, nicorandil, and ivabradine.

3. * Coronary revascularization.* The use of percutaneous coronary intervention and coronary artery bypass surgery will be documented at 6 weeks and 6 months.

### Long-term outcomes

Annual hospitalizations for chest pain episodes, acute coronary syndromes, coronary revascularization procedures, cerebrovascular disease and peripheral vascular disease will be recorded from the Information and Statistics Division of NHS Scotland, and deaths from the Central Registry Office, Scotland for up to 10 years following trial enrolment. Where possible, events will be corroborated by electronic hospital records and case note review.

### Diagnosis and management documentation

The CT scan report will include a section requesting the documentation of any changes in the diagnosis, investigation and treatment of the participant. The chest pain clinic nurse or responsible consultant will complete this pro forma and return it to the trial manager.

At 6 months, trial and data manager will document changes in patient diagnosis, investigation and treatment for all patients at 6 weeks and 6 months using the TrakCare™ software application (InterSystems Corporation, Cambridge, MA, USA), which is an electronic patient record system used by the National Health Service (NHS) Lothian Health Board. This system is destined to be adopted by other centres throughout Scotland. Where appropriate, this will be supplemented by source document review.

### Safety outcomes

#### Radiation dose

The main safety concerns relate to exposure to ionizing radiation [25]. The dose-length product (DLP) will be recorded and the effective radiation dose will be calculated using the conversion factor method. Age- and sex-specific lifetime attributable risks of cancer will be estimated using the Biological Effects of Ionizing Radiation VII Phase 2 report [26]. All incident cancers identified during the study will be recorded throughout the follow-up phase of the trial.

#### Incidental findings

Incidental findings occur in 22 to 74% of CT scans of the chest but only 1.7% of these are clinically significant [27]. Nevertheless, any incidental findings may require further investigations, involving exposure to ionizing radiation. An incidental finding will be defined as an abnormality identified on CT without antecedent clinical suspicion or previously known disease [27]. The presence of incidental findings will be documented at the time of the initial CT coronary angiography and any further investigations be documented by review of the participant’s medical records.

#### Data analysis

The trial results will be reported in accordance with the CONSORT guidelines and, where possible, the clinical profile of unrecruited and ineligible patients will be recorded.

#### Statistical analysis

The trial statistician will supervise statistical analyses performed by Edinburgh Clinical Trials Unit. A full statistical analysis plan will be written separately.

#### Sample size

Previous studies have diagnosed angina pectoris in 27.0% of clinic attendees [6]. Whilst CT coronary angiography may reduce ‘false-positive’ diagnoses of angina; this intervention is most likely to increase the diagnosis of angina, given that current standard diagnostic approaches tend to be conservative and under-diagnose coronary heart disease [6]. We believe that, to be clinically useful, this intervention should increase the clinical diagnosis of angina due to coronary heart disease in at least 1 in 25 clinic attendees. For 80% power at a two-sided *P* value of 0.05, we will need to recruit 2,069 patients per group to detect an absolute increase of 4.0% in the diagnosis of angina.

#### Sample size: long-term outcome

Establishing the diagnosis of angina is an important aspect for the trial but ultimately it is the long-term patient outcome that is important; can patients’ chest pain symptoms be resolved and their long-term outcome improved? After 5 years of follow-up, we would anticipate a coronary event rate (coronary heart disease death or acute coronary syndrome) of 13.1% for the total population [6]. The study would have 80% power at a two-sided *P* value of 0.05 to detect a decrease of 2.8% in the 5-year event rate. This would also provide ~600 events and permit the exploration of up to 60 variables [28] in evaluating the predictive value of established risk factors and the novel risk factors of coronary artery calcium score and CT coronary angiography.

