### Patient population

Participants will be identified from patients attending the rapid access chest pain clinic. We will recruit 4,138 patients, randomized 1:1 to standard care (*n* = 2,069) or standard care with coronary calcium score and CT coronary angiography (*n* = 2,069).

Inclusion criteria will be: (i) attendance at the rapid access chest pain clinic and (ii) age over 18 years but less than or equal to 75 years.

Exclusion criteria will be: (i) inability or unwillingness to undergo CT scanning; (ii) exceeding the weight tolerance of scanner; (iii) known severe renal failure (serum creatinine >200 μmol/l or estimated glomerular filtration rate <30 ml/min); (iv) previous recruitment to the trial; (v) major allergy to iodinated contrast agent; (vi) inability to give informed consent; (vii) known pregnancy; or (viii) acute coronary syndrome within 3 months.

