### Randomization

Following recruitment, patients who agree to undergo research evaluation will be randomized (1:1), either to no additional scanning or to undergo further evaluation with coronary calcium scoring and CT coronary angiography within 14 days of clinic attendance and before invasive coronary angiography or other cardiac investigations. Randomization will be conducted using a web-based system to ensure allocation concealment and will incorporate minimization to ensure matching for age, sex, body mass index (height and weight), diabetes mellitus, prior history of coronary heart disease, atrial fibrillation and baseline diagnosis of angina due to coronary heart disease.

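### The long-term sample-size paragraph overstates the events and variables available for risk modelling, most of all for models that contain the CT predictors

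*Protocol article*

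**What the plan says.** All of the following is in the protocol article.

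- Patient population: "We will recruit 4,138 patients, randomized 1:1 to standard care", with 2,069 in each arm.
- Sample size: long-term outcome, event rate at 5 years: "we would anticipate a coronary event rate (coronary heart disease death or acute coronary syndrome) of 13.1% for the total population".
- Same section, power: "The study would have 80% power at a two-sided *P* value of 0.05 to detect a decrease of 2.8% in the 5-year event rate".
- Same section, risk modelling: "This would also provide ~600 events and permit the exploration of up to 60 variables". The sentence goes on to name the predictors as "established risk factors and the novel risk factors of coronary artery calcium score and CT coronary angiography". One allowance covers both sets.
- Randomization: patients are allocated "either to no additional scanning or to undergo further evaluation with coronary calcium scoring and CT coronary angiography within 14 days" of the clinic visit. The Equipoise section bars clinic doctors from ordering CT coronary angiography for patients not randomized to it.
- Study objectives: one stated long-term aim is to find out whether CT assessments are independent predictors of later risk.

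**The concern.** There are two separate problems with one sentence.

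First, the event count should be the number of patients multiplied by the anticipated rate. Both numbers are in the article, and their product is not close to 600. The variable allowance is derived from the event count and falls with it.

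Second, the sentence counts events across the whole trial but applies the count to "novel risk factors of coronary artery calcium score and CT coronary angiography". By design these are not measured in the standard-care arm, so a model that includes them can draw on only about half the patients.

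At stake is the prognostic aim in Study objectives. This paragraph is where the article states how much information that aim will have. An analyst who took the allowance at face value could plan a CT model with more candidate variables than its events support at the article's own ratio.

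**Working it through.** **Inputs**

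- N = 4,138, with 2,069 per arm (Patient population).
- 5-year event rate 13.1%; detectable decrease 2.8 points; 80% power; two-sided 0.05 (Sample size: long-term outcome).
- Stated: about 600 events and up to 60 variables (same section).
- Assumption: no loss to follow-up, since none is stated for this outcome. Any loss would lower the counts below.

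**Step 1. Reproduce the power statement.** Take 13.1% as the control rate, so the CT arm is at 13.1% − 2.8 = 10.3%. With the usual normal approximation for two proportions and no continuity correction, 2,068 patients per arm are needed, and 2,069 per arm give 80.0% power. The power statement therefore reproduces, which indicates that the paragraph's working scenario is 13.1% against 10.3%.

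**Step 2. Events in the whole trial.**

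- 13.1% throughout: 4,138 × 0.131 = 542. The stated 600 is 600/542 = 1.107 times this, about 11% too high.
- 13.1% against 10.3%: 2,069 × (0.131 + 0.103) = 484. The stated 600 is 600/484 = 1.24 times this, 24% too high.

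**Step 3. What would produce 600?**

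- An overall rate of 600/4,138 = 14.5%, or 600/0.131 = about 4,580 patients. Neither is in the article.
- 15.9% against 13.1% gives 2,069 × (0.159 + 0.131) = 600. Power for that pairing is 72.5%, and 13.1% would then be the CT-arm rate, not the rate for the total population.
- If 13.1% is the average of the two arms (14.5% and 11.7%), the total is 542 again and power is 76.1%.

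None of these scenarios satisfies the rate, the power and the event count together.

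**Step 4. Variables in the whole trial.** The implied ratio is 600/60 = 10 events per variable. Then 542/10 gives about 54 variables and 484/10 about 48.

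**Step 5. Events and variables for models with CT predictors.** At most 2,069 patients contribute.

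| CT-arm 5-year rate | Events | Variables at 10 events each | Events per variable if 60 were used |
|---|---|---|---|
| 13.1% (no effect) | 2,069 × 0.131 = 271 | 27 | 4.5 |
| 11.7% (13.1% as the average) | 2,069 × 0.117 = 242 | 24 | 4.0 |
| 10.3% (powered decrease) | 2,069 × 0.103 = 213 | 21 | 3.6 |

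These counts are ceilings. The Medication section says CT angiography will not be performed if the heart rate stays above 100 beats per minute despite rate-limiting medication. The article does not say how many patients that will be.

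**The case against.** **The figures are hedged.** The sentence uses an approximation sign, sets an upper limit on variables and speaks of exploration. This partly stands: against 542 events the overstatement is about 11%, and the allowance moves only from 60 to 54. The hedge does not reach 484, still less 213 to 271.

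**484 is only one scenario.** This is fair. The article calls 13.1% the rate for the total population, which gives 542, while the power statement fits 13.1% as the control rate, which gives 484. Both should be shown, and the figure of 600 fits neither.

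**Established risk factors are not confined to the CT arm.** This stands. Models of those factors alone can use the whole-trial count, so the halving applies only to models with CT variables.

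**Linkage runs for up to 10 years (Long-term outcomes), so more events may accrue.** This is true, but the sentence rests on a 5-year rate and the section gives no later one.

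**The ratio of 10 is inferred.** This is correct. It comes from dividing 600 by 60; the article cites a source for the allowance but does not state the rule. The comparison here is with the article's own ratio and does not claim that 10 is the right threshold.

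**A stronger reading that the article does not support.** A reader might infer that a 60-variable model in the CT arm is planned and will be overfitted. The article proposes no such model. It names two predictor sets under one allowance and does not say that all 60 variables would enter a single CT-arm model. Overfitting is a risk if the allowance were used in that way, not a certain result.

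**Conclusion.** The concern holds, at moderate severity. The article's inputs give about 484 to 542 events at 5 years, not about 600, and support about 48 to 54 variables at the implied ratio. For models containing calcium score or CT angiography, the ceiling is about 213 to 271 events and 21 to 27 variables. Applied to such a model, the stated allowance would be 60/27 = 2.2 to 60/21 = 2.9 times what that ratio supports.

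This rests on the stated 13.1% rate, full recruitment, complete 5-year follow-up and the inferred ratio of 10.

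It would be wrong to infer that the trial is mis-sized. The 2,069 per group comes from the 6-week diagnosis endpoint (Sample size), and the long-term power statement reproduces. The error is confined to the information claimed for an exploratory secondary aim.

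**What to change.** Replace the single sentence in Sample size: long-term outcome with two statements:

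1. For models of established risk factors in all patients: about 480 to 540 events at 5 years, supporting about 48 to 54 variables at 10 events per variable.
2. For models that include calcium score or CT angiography: at most about 210 to 270 events at 5 years, supporting at most about 21 to 27 variables at the same ratio. Note that these are ceilings because some CT-arm patients will not be scanned.

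State the 10-per-variable ratio openly, and say whether 13.1% is the control rate or the overall rate. Rules on how to count categories or coronary segments as parameters can be left to the statistical analysis plan.

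The cost is a text change. Design, recruitment, data collection and the power statement are untouched; the stated modelling capacity becomes less favourable.

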#### Statistical analysis plan

Where appropriate, two main comparisons will be made: (a) between the scanned and unscanned groups; and (b) in the scanned group only, between the initial clinic assessment and the final assessment following knowledge of the CT scan. The primary analysis will be a comparison between the scanned and unscanned groups, of the proportion of patients diagnosed with angina pectoris secondary to coronary heart disease at 6 weeks. This comparison will be performed using logistic regression, adjusted for the variables in the minimization algorithm.

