**Methods/design:**

The SCOT-HEART study is an open parallel group prospective multicentre randomized controlled trial of 4,138 patients attending the rapid access chest pain clinic for evaluation of suspected cardiac chest pain. Following clinical consultation, participants will be approached and randomized 1:1 to receive standard care or standard care plus ≥64-multidetector computed tomography coronary angiography and coronary calcium score. Randomization will be conducted using a web-based system to ensure allocation concealment and will incorporate minimization. The primary endpoint of the study will be the proportion of patients diagnosed with angina pectoris secondary to coronary heart disease at 6 weeks. Secondary endpoints will include the assessment of subsequent symptoms, diagnosis, investigation and treatment. In addition, long-term health outcomes, safety endpoints, such as radiation dose, and health economic endpoints will be assessed. Assuming a clinic rate of 27.0% for the diagnosis of angina pectoris due to coronary heart disease, we will need to recruit 2,069 patients per group to detect an absolute increase of 4.0% in the rate of diagnosis at 80% power and a two-sided *P* value of 0.05. The SCOT-HEART study is currently recruiting participants and expects to report in 2014.

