### Primary endpoint

The primary endpoint of the study will be the proportion of patients diagnosed with angina pectoris secondary to coronary heart disease at 6 weeks. The clinician in charge of the patients’ care will assign the diagnosis following either (a) analysis of the coronary artery calcium score and CT coronary angiogram (intervention group), or (b) standard care (conservative group).

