#### Computed tomography

Computed tomography scans will be performed using a 64, 128 or 320-multidetector scanner. Computed tomography protocol optimizations will be performed at all sites throughout the study, to optimize scanning parameters, such as radiation dose and contrast administration.

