### Trial status

The study has been approved by the South East Scotland Research Ethics Committee. Recruitment is underway at eight sites. At present, 1000 participants have been recruited to the SCOT-HEART study.

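### Study centre is in neither the minimization list nor the stated primary logistic model; adding it to the model is a small, nearly free gain

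*Protocol article*

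**What the plan says.** The Methods part of the abstract describes an "open parallel group prospective multicentre randomized controlled trial of 4,138 patients". The Trial status section adds: "Recruitment is underway at eight sites".

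The Randomization section gives the minimization factors: "matching for age, sex, body mass index (height and weight), diabetes mellitus, prior history of coronary heart disease, atrial fibrillation and baseline diagnosis of angina". The last item refers to angina attributed to coronary disease. That makes seven factors, and centre is not one of them.

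The Statistical analysis plan section of the article sets the primary comparison, which is the proportion diagnosed with angina due to coronary heart disease at 6 weeks. It states: "This comparison will be performed using logistic regression, adjusted for the variables in the minimization algorithm". Read together, the two sections give a primary model with treatment and those seven factors, and no centre term.

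The Primary endpoint section says the clinician responsible for the patient's "care will assign the diagnosis following either" review of the CT results or standard care. The trial is open and no central adjudication is described. The Diagnosis and management documentation section says 6-week changes in diagnosis are recorded at 6 months from one electronic record system. That system is described as belonging to one health board and expected to spread to other Scottish centres, with source documents reviewed where appropriate.

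**The concern.** The outcome depends partly on where a patient is seen. Clinicians' thresholds for calling chest pain angina can differ between clinics, and so can the completeness of the records from which the 6-week diagnosis is taken. Both act in both arms, which makes centre a candidate prognostic factor for this endpoint. The protocol accepts centre differences elsewhere: the health economic analysis uses centre-specific costs.

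Leaving a prognostic factor out of a logistic model has two consequences. The treatment odds ratio is then averaged over that factor, which places it nearer to 1 than the odds ratio within centres. The test also loses some power. The trial is planned at 80% power, so a point or two is worth having if it costs almost nothing.

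**Working it through.** **Inputs from the Sample size section.** Control rate 27.0%, absolute increase 4.0 points (so 31.0%), two-sided 0.05, 80% power, 2,069 per group.

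**Assumed input.** The between-centre SD of the log odds of diagnosis is not in the documents. It is varied from 0.1 to 1.0.

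**Step 1: reproduce the plan's figure.** The two-proportion formula with pooled variance under the null gives

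n = [1.96 × √(2 × 0.29 × 0.71) + 0.8416 × √(0.27 × 0.73 + 0.31 × 0.69)]² / 0.04² = 2,019.

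The continuity correction, n/4 × [1 + √(1 + 4/(0.04 n))]², gives 2,069. The stated size is reproduced exactly.

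**Step 2: model without centre.**
- Odds ratio = (0.31/0.69)/(0.27/0.73) = 1.215; log odds ratio = 0.1945.
- Standard error = √[1/(2,069 × 0.27 × 0.73) + 1/(2,069 × 0.31 × 0.69)] = 0.0686.
- Power = Φ(0.1945/0.0686 − 1.96) = 80.9%.

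**Step 3: model with centre.** Give each centre a normal intercept on the log-odds scale with the assumed SD. Hold the overall rates at 27% and 31% and solve by numerical integration for the within-centre log odds ratio b. Its information is the average over centres of 2,069 × v0·v1/(v0 + v1), where v = p(1 − p) in each arm. At SD 0.5, for example, b = 0.2042 with standard error 0.0703. Attenuation is then 1 − 0.1945/0.2042 = 4.75%, and power is Φ(0.2042/0.0703 − 1.96) = 82.7%.

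| SD | 95% range of centre control rates | Odds ratio given centre | Log odds ratio smaller without centre by | Power with centre (80.9% without) |
|---|---|---|---|---|
| 0.1 | 23% to 31% | 1.215 | 0.2% | 81.0% |
| 0.2 | 20% to 35% | 1.217 | 0.8% | 81.2% |
| 0.3 | 17% to 40% | 1.219 | 1.8% | 81.6% |
| 0.5 | 12% to 48% | 1.227 | 4.8% | 82.7% |
| 0.75 | 7% to 59% | 1.241 | 9.8% | 84.7% |
| 1.0 | 4% to 68% | 1.259 | 15.5% | 86.9% |

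**Step 4: check by simulation.** Logistic models were fitted with and without centre to 4,138 simulated patients in 12 centres, 400 runs per setting.
- With no other covariate, attenuation was 2.4%, 5.0% and 16.1% at SD 0.3, 0.5 and 1.0.
- With a strong baseline-diagnosis covariate in both models (assumed prevalence 27%, log odds coefficient 3), it was 1.5%, 4.0% and 13.3%. Here the SD is what remains after that adjustment. Power without and with centre was 92.7% and 92.5%, 96.3% and 97.0%, and 93.8% and 97.5%.

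Attenuation is therefore similar once baseline diagnosis is in the model. The power gain at SD 0.3 to 0.5 is smaller there, under 1 point, because power is already near its ceiling.

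**Step 5: cost of the centre terms.** Expected events are 2,069 × (0.27 + 0.31) = 1,200. Eight sites need seven fixed-effect terms, which that number carries easily.

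**The case against.** **The analysis plan is separate.** The article defers a full statistical analysis plan, and handling of centre is often settled there. This weakens the point but does not remove it. The article already states the adjustment set for the primary model, so a plan that included centre would have to depart from it.

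**The effect is not bias.** A reader might infer that the odds ratio is needlessly attenuated, or that the result would be biased. The documents support neither. The size of any attenuation depends on an SD they do not give. The shift is non-collapsibility: the two models estimate different odds ratios, one averaged over centres and one within them. The comparison of proportions, which the article names as the primary comparison, is unaffected. Under no treatment effect both odds ratios equal 1. Because centre is not a minimization factor, leaving it out of the model does not make the standard errors wrong. This objection stands.

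**Baseline diagnosis absorbs part of the site effect.** The model already adjusts for it, and it too is a local clinician's judgement. That is right, and it makes residual SDs near 1.0 hard to defend.

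**Scanners.** It is tempting to argue that scans are "performed using a 64, 128 or 320-multidetector scanner", so sites differ and centre must be in the model. The article does not say which site has which scanner. Scanning also happens only in the CT arm, so such differences would mainly show as treatment-by-centre heterogeneity, which a centre main effect does not remove. The same holds for local CT reporting. Neither supports this point.

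**Record capture.** The record system was expected to reach other centres and is supplemented by source documents, so a difference in capture is possible rather than shown.

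**Chance imbalance and minimization.** A reader might also want centre added to the minimization. With 4,138 patients randomized 1:1, chance imbalance by centre is small and is already reflected in the standard errors. About 1,000 patients had been randomized, and in an open trial minimizing within centre can make allocations easier to predict. Leaving centre out of the minimization is defensible.

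**Conclusion.** The point holds as a minor one. The stated primary model has no centre term, although the endpoint is a local, unblinded diagnosis in a multicentre trial. At the protocol's design effect, and for an assumed between-centre SD of 0.3 to 0.5, leaving centre out makes the log odds ratio about 2% to 5% smaller and costs about 1 to 2 points of power, or less where baseline diagnosis is strongly prognostic. A loss near 15% and 6 points needs an SD of 1.0, with centre control rates running from about 4% to 68%. If centres hardly differ, there is next to nothing to gain and next to nothing to lose. Validity of the test and of the comparison of proportions is not in question. The calculation assumes normally distributed centre intercepts and the same treatment odds ratio in every centre.

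**What to change.** In the Statistical analysis plan section, extend the adjustment set to the minimization variables plus study centre, as fixed effects or a random intercept. Use the same set in the between-arm models for the secondary endpoints. If the sponsor prefers to leave centre out, give the reason. Settle this before the data are seen, so that the choice cannot depend on the result.

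The cost is one phrase. A multicentre trial already knows each patient's centre, so no new data are needed. Leave the minimization unchanged.
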